### Sample/participants

2.3

Subjects will be recruited using emails, letters and flyers circulated in a southeastern university, its academic medical center and the surrounding metropolitan area. Email communications will be managed by institutional mass‐email distribution services and will prioritize prospective participants who have expressed an interest in participating to either a participating physician or a recruitment platform such as ResearchMatch, a national health volunteer registry that was created by several academic institutions and supported by the U.S. National Institutes of Health as part of the Clinical Translational Science Award (CTSA) program. Recruitment letters will be mailed to prospective participants who have either expressed interest in the study to their physician or were identified as candidates through chart review. Flyers will be posted throughout the medical center and will adhere to IRB guidelines outlining transparency and undue coercion; furthermore, these flyers will also be posted throughout the surrounding area at community centers and assisted living facilities. Because we are interested in the continuous measure of age, we will enroll 60 subjects to yield a final continuous sex‐balanced stratified sample of adults aged 30–89. We will stratify by age range (to allot 5 males/5 females) to each of six age strata: 30–39, 40–49, 50–59, 60–69, 70–79, 80–89. We will identify females who are pre‐ and post‐menopausal to control for hormone status on psychophysical and neurophysiological pain.

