#### Psychophysical testing (Aim 1)

2.4.2

Using the Medoc PATHWAYS Pain and Sensory Evaluation System (Medoc Ltd., Israel), a thermal stimulus will be delivered in degrees Celsius (°C; starting at 30°C and ramping upward at a rate of 1°C/s) to the thenar eminence of the right hand. We will deliver the thermal stimuli necessary to produce a subjective report of just noticeable pain (JNP), weak pain (WP) and moderate pain (MP). Three trials of each of the three levels of stimuli will be obtained and a single average score for JNP, WP and MP will be recorded for each subject. Next the average temperature will be administered and participants will be immediately be asked to provide an unpleasantness (affective) rating for each percept ranging from 0–20 where 0 indicates neutral and 20 indicates severely distressing for JNP, WP and MP (Petzke, Harris, Williams, Clauw, & Gracely, 2005).

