#### Sample size estimation

2.6.4

Case/control groups of the size proposed in this research (30 younger adults, 30 older adults) will provide 80% statistical power to detect a difference in outcomes of interest as small as half a standard deviation in the distributions of the observed values. This represents a large difference in terms of the expected control values. Given that this is a preliminary exploratory study, we want to focus on detecting larger effects. For example, assuming that we find that the younger group reports that mild pain is experienced on average at 35°C (*SD* 6°C) with a corresponding unpleasantness rating of mean 9.2 (*SD* 4.0), our group sizes can detect an increase in the temperature level for mild pain in the older group as small as 3°C and a difference in unpleasantness ratings as small as 2 scale points. The same logic will hold for the activation and functional connectivity age group analyses. Using data from previous ageing research (Cole et al., 2006, 2010) we can expect that our control participants may have activation values (as Z scores) with approximate *mean* = 3.81 and *SD* 0.46. Given our proposed sample sizes, a respective case activation mean value of ~4.04 would be statistically significant. Correlations between observed values (e.g., pain, age, depression, anxiety, and activation in an ROI) as small in absolute value as 0.34 will be statistically significant (*p* < .05).

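### Thirty versus thirty gives about 48% power for a half-SD difference, not the stated 80%; the 80% point is about 0.74 SD

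*Protocol article*

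**What the plan says.** Section 2.6.4 of the protocol article bases its calculation on "Case/control groups of the size proposed in this research (30 younger adults, 30 older adults" and claims that these numbers "will provide 80% statistical power to detect a difference in outcomes of interest as small as half a standard deviation". The yardstick is "half a standard deviation in the distributions of the observed values", so it is the between-person SD of the outcome, not the SD of paired differences or of averaged measurements.

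Four illustrations follow:

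- a detectable rise of 3°C in the mild-pain temperature, with SD 6°C;
- a detectable difference of 2 unpleasantness points, with SD 4.0;
- for activation, with mean 3.81 and SD 0.46, that "a respective case activation mean value of ~4.04 would be statistically significant";
- that correlations "as small in absolute value as 0.34 will be statistically significant" at p < .05.

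Section 2.6 (Data analysis) caps alpha at 0.05 without stating sidedness, and makes the interaction of continuous age with sex the primary effect. Section 2.3 (Sample/participants) states that "we will enroll 60 subjects to yield a final continuous sex‐balanced stratified sample of adults aged 30–89", with 5 males and 5 females in each of six age strata.

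**The concern.** Thirty per group is well short of what a half-SD difference usually needs for 80% power, and the three mean-difference illustrations are all the same 0.5 SD in different units. The section also moves between two ideas: a true difference that the study has an 80% chance of finding, and an observed difference that would just be significant. At this sample size the second is close to half an SD and the first is much larger.

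At stake is what the study is said to be able to show. A reader who takes section 2.6.4 at face value would give a null younger-versus-older comparison more weight against half-SD differences than it can bear.

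**Working it through.** **Inputs.** n = 30 per group, independent groups, difference 0.5 SD, claimed power 80%, SDs of 6°C, 4.0 points and 0.46, and activation mean 3.81 (all section 2.6.4); alpha 0.05 (section 2.6). Two-sided testing is my assumption; one-sided results are given as well.

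**1. The plan's 80%.** The noncentrality is δ = d·√(n/2) = 0.5·√15 = 1.936. The two-sided critical t on 58 df is 2.002.
- Noncentral t, two-sided: power 47.8% (normal approximation 49.1%).
- Noncentral t, one-sided: power 60.6% (normal approximation 61.5%).

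The stated 80% does not reproduce on either basis. For d = 0.5, 80% power needs 63.8, so 64 per group two-sided, or 51 per group one-sided.

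**2. The worked examples.** 3/6 = 0.5; 2/4.0 = 0.5; (4.04 − 3.81)/0.46 = 0.23/0.46 = 0.5. The temperature and unpleasantness examples are presented as detectable differences, so each has about 48% power.

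**3. What 80% power does detect.** Solving the noncentral t for n = 30 per group gives d = 0.736 two-sided (0.650 one-sided). In the plan's units, two-sided:
- temperature: 0.736 × 6 = 4.4°C;
- unpleasantness: 0.736 × 4.0 = 2.9 points;
- activation: 3.81 + 0.736 × 0.46 = 4.15.

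**4. Where half an SD comes close.** The smallest observed difference significant at the two-sided 5% level is t·√(2/n) = 2.002 × √(2/30) = 0.517 SD. An observed difference of exactly 0.5 SD gives t = 1.936 and p = 0.058. For activation the threshold is 3.81 + 0.517 × 0.46 = 4.048 by t, or 3.81 + 1.96 × √(2/30) × 0.46 = 4.043 by the normal approximation.

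**5. Could an unstated feature restore 80%?**
- Pairing: a paired or one-sample test on 30 gives 75% (t) or 78% (normal), but younger and older adults are separate people.
- Covariates: they would have to explain 1 − (0.5/0.736)² = 54% of outcome variance.
- Averaging three measures: 80% is reached only if their correlation is about 0.2; at 0.5, power is 65%.

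Section 2.6.4 invokes none of these.

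**6. Correlations.** The smallest significant |r| at n = 60 is t/√(t² + 58) = 2.002/√(4.007 + 58) = 0.254. The true |r| with 80% power is tanh[(1.960 + 0.842)/√57] = 0.355. The stated 0.34 is neither: as a significance threshold it corresponds to n of about 34, and as a true value it has 76% power at n = 60. The error is conservative, since r = 0.34 at n = 60 gives t = 0.34·√(58/(1 − 0.34²)) = 2.75 and p = 0.008.

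**The case against.** The strongest defence is that the study is labelled preliminary and exploratory, and that section 2.6 analyses age as a continuous variable, so a two-group t-test understates what will be done. Part of this stands. Assume ages spread uniformly over 60 years and a linear trend that puts the two age halves 0.5 SD apart. The slope is then 0.5/30 SD per year and the age SD is 60/√12 = 17.3 years, so the age effect is 17.3 × 0.5/30 = 0.289 SD. The noncentrality is about 0.289 × √60 = 2.24, and power is about 60%. A reader might therefore infer too much from the 48% by saying that the study as a whole will miss half-SD effects more often than not. That holds only for the two-group comparison that section 2.6.4 describes. Even so, 60% is not 80%, and an exploratory label does not make a stated power figure correct.

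Other stronger readings are not supported:

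- **That the activation figure is a comparable error.** The sentence speaks of significance, not power, and carries an approximation sign. The normal threshold of 4.043 rounds to the stated value. The exact t threshold is slightly higher, and the fault is mainly that a significance threshold stands beside power claims without a label.
- **That results would be misclassified against 0.34.** Sections 2.6 and 2.6.2 judge significance by p-value; 0.34 is a planning illustration, not a cutoff.
- **That n = 60 has no other basis.** Section 2.3 gives a design reason, equal numbers by sex in six age strata.
- **That the assumed mean of 35°C is incompatible with a ramp starting at 30°C.** The mean is an illustrative assumption and enters no power figure; only the ratio 3/6 does. The distributional argument would also need normality, which the article does not claim.

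**Conclusion.** The 80% claim is wrong on the article's own inputs. For 30 versus 30 at alpha 0.05, power at 0.5 SD is 48% two-sided, an overstatement of 32 percentage points, or 61% one-sided, an overstatement of 19. The 3°C and 2-point examples carry the same error; their 80%-power counterparts are about 4.4°C and 2.9 points (3.9°C and 2.6 points one-sided). The section appears to treat a value near the significance threshold as if it were the difference detectable with 80% power.

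This rests on independent groups, equal SDs, 30 complete cases per group and no unstated gain in precision. The correlation point is minor and errs on the safe side. Correcting these figures would still not give the power of the age-by-sex interaction, because section 2.6.4 contains no calculation for it.

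**What to change.** Restate section 2.6.4 as follows:

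- With 30 per group and two-sided alpha 0.05, 80% power applies to differences of about 0.74 SD (about 4.4°C and 2.9 unpleasantness points). Power at 0.5 SD is about 48%.
- An observed activation mean of about 4.05 is the significance threshold; a true mean of about 4.15 is detectable with 80% power.
- At n = 60 the smallest significant |r| is about 0.25, and a true |r| of about 0.355 has 80% power.
- These figures concern the younger-versus-older contrast and simple correlations, not the age-by-sex interaction named as primary in section 2.6.

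This is a change of wording only. Enrolment, procedures and analyses stay as they are; the cost is that the stated figures become less favourable.

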### Data analysis

2.6

Statistical approaches for the analysis of the psychophysical and neurophysiological data will mirror each other. Age (continuous) and sex (male, female), and a term specifying the interaction of age and sex will be entered into general linear modeling modules in SPSS (psychophysical) and SPM (neurophysiological). We are hypothesizing different patterns of association of age with psycho‐ and neurophysiological data for males and females therefore the interaction term will be the primary effect of interest in these analyses. Main effects of ageing and sex will be tested; however, they will serve as covariates in the primary analyses. All data distributions will be evaluated and transformed as needed to meet the assumptions of the specific statistical methods. All statistical significance tests will maintain Type I error rates (alpha values) of no more than 0.05.

#### Aim 1

2.6.1

The temperature at which JNP, WP, and MP is perceived (Aim 1, Hypothesis 1), and the subject's respective affective rating of the pain (Aim 1, Hypothesis 2) at each sensory level, comprise the key dependent variables for Aim 1. Descriptive and graphical summaries of the temperatures (intensities) and affective (unpleasantness) ratings will be generated at each of the three self‐reported sensory thresholds (JNP, WP, and MP), and for each of the stratified levels of age, to inform linear and possible nonlinear associations of age with the intensity and unpleasantness sensations. Linear mixed effects analysis incorporating robust variance estimation (i.e., generalized estimating equations) will be used to test the hypotheses that for a given self‐reported sensory threshold, temperatures are higher, and ratings of unpleasantness are lower with increasing age. This effect would be indicated by a statistically significant interaction of age level with self‐reported sensory level on the dependent variables (Aim 1, Hypothesis 1: temperature; Aim 1, Hypothesis 2: unpleasantness rating). A statistically significant linear or nonlinear association of age with those variables but no interaction effect will indicate an age effect on temperature and unpleasantness regardless of perceived pain.

#### Aim 2

2.6.2

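### The illustrative mild-pain temperature (mean 35°C, SD 6°C) is implausible for a ramp that starts at 30°C, so the 3°C detectable difference has no sound basis in either direction

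*Protocol article*

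**What the plan says.** Section 2.4.2 (Psychophysical testing) defines how the Aim 1 temperature is measured. A thermode delivers heat "starting at 30°C and ramping upward at a rate of 1°C/s". The temperature is noted at just noticeable, weak and moderate pain. "Three trials of each of the three levels of stimuli will be obtained", and the average at each level is the participant's score.

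Section 2.6.4 (Sample size estimation) works with two groups, "30 younger adults, 30 older adults", and claims "80% statistical power to detect a difference in outcomes of interest as small as half a standard deviation". It then gives an example in degrees. If, in the younger group, "mild pain is experienced on average at 35°C (*SD* 6°C"), then "our group sizes can detect an increase in the temperature level for mild pain in the older group as small as 3°C". The 3°C is half of 6°C. No source is given for the temperature pair, whereas the activation values in the same section are attributed to earlier ageing research.

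Section 2.6 (Data analysis) sets the error rate: "All statistical significance tests will maintain Type I error rates (alpha values) of no more than 0.05". It does not say whether tests are one- or two-sided. It states no distribution for the temperatures and allows transformation where needed.

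**The concern.** Every trial starts at 30°C and the temperature only rises. No single threshold can be below 30°C, and neither can an average of three. The assumed mean lies 5°C above that floor, while the assumed SD is 6°C. A standard deviation larger than the whole distance from the mean to a hard lower bound is possible, but only for a very skewed variable.

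The 3°C is the only detectable difference that the article gives in degrees. A reader would use it to judge which younger-versus-older difference in pain temperature the study could find. If the inputs do not describe the endpoint as measured, the 3°C cannot serve that purpose, and correcting the power arithmetic alone would carry the same doubtful SD into the new figure.

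**Working it through.** **Inputs.** Mean 35°C, SD 6°C, 30 per group, 80% power and 3°C come from section 2.6.4. The 30°C floor comes from section 2.4.2 and alpha 0.05 from section 2.6. Two-sided testing is my assumption; one-sided results are given where they matter.

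**1. The plan's own figure.** The 3°C is 0.5 × 6. The noncentrality is (3/6) × √(30/2) = 1.936.
- Normal approximation, two-sided: power = Φ(1.936 − 1.960) = 49.1%. The t-test gives 47.8%.
- One-sided: 61.5% (t-test 60.6%).

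The stated 80% does not reproduce. At SD 6 the difference detectable with 80% power is 6 × √(2/30) × (1.960 + 0.842) = 4.34°C (t-test 4.41°C), or 3.90°C one-sided by t-test. The printed 3°C is close to the smallest observed difference that would just reach two-sided significance, 3.10°C.

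**2. The floor under a normal model.** (30 − 35)/6 = −0.833 and Φ(−0.833) = 20.2%, or about 6 of 30 younger participants. Cutting the normal distribution at 30°C does not give back the printed pair: truncated, it has mean 37.1 and SD 4.57; with values below 30°C set to 30°C, it has mean 35.7 and SD 4.98.

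**3. The floor under skewed models (assumed shapes).** Both have mean 35, SD 6 and no values below 30°C.
- Shifted gamma: shape (5/6)² = 0.694, scale 36/5 = 7.2. The density is highest at the starting temperature, the median is 32.9°C, and 26% of participants lie below 31°C. At 1°C/s, that is pain within the first second.
- Shifted lognormal: median 33.2°C, lower quartile 31.7°C. A quarter report pain within about 1.7 seconds.

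**4. What other SDs would imply.** Mean kept at 35°C, normal model, 30 per group, two-sided 0.05, t-test; detectable difference = 0.736 × SD. Only SD 6 is in the article; the other SDs are assumptions.

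| SD (°C) | Share below 30°C | Power for 3°C | Detectable at 80% power (°C) |
|---|---|---|---|
| 6 | 20.2% | 47.8% | 4.41 |
| 5 | 15.9% | 62.8% | 3.68 |
| 4 | 10.6% | 81.5% | 2.94 |
| 3 | 4.8% | 96.8% | 2.21 |
| 2.5 | 2.3% | 99.5% | 1.84 |

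A difference of 3°C reaches 80% power at SD ≤ 3/0.736 ≈ 4.1°C.

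**5. The other way to resolve the conflict.** Keep SD 6 and raise the mean. For at most 2.5% below the floor, the mean must be at least 30 + 1.96 × 6 ≈ 41.8°C. The detectable difference then stays at about 4.4°C.

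**The case against.** The strongest reply is that the article never states normality, so nobody has to fall below 30°C, and section 2.6 allows transformation. That is right: a reader might infer that a fifth of the younger group must feel pain below the starting temperature, but this follows only under a normal model. The skewed alternatives are nevertheless hard to believe for an average of three trials. On a transformed scale, 3°C would no longer be half an SD.

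Skew alone also does little harm to a comparison of means. Simulation of 30 versus 30 with floor-bounded distributions (mean 35, SD 6) gave 52% power for a 3°C shift with a shifted gamma and 59% with a shifted lognormal, against 48% under normality. This stands. The difficulty is whether mean 35 with SD 6 describes this endpoint at all, not whether the t-test tolerates skew.

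A reader might also infer that the SD is the wrong member of the pair, or that the study is underpowered on this ground. The documents support neither. A higher mean with SD 6 also fits the ramp, and a smaller SD would make 3°C easier to detect.

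Three further points stand and limit the weight of the concern. The figures are offered as an example and the sizing claim comes first in SD units. Section 2.6 makes the age-by-sex interaction the effect of main interest, so a younger-versus-older contrast never measured what that test can detect. The term mild pain is not tied to any of the three defined levels, so no argument should rest on its being above just noticeable pain. A missing source is likewise something a condensed article may leave to the full protocol. It matters here only because, without it, the reader cannot tell which value is wrong.

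**Conclusion.** The point holds against the mean and SD as a pair. Given an upward ramp from 30°C, mean 35°C with SD 6°C is implausible: 20.2% of a normal distribution lies below the floor, and skewed shapes with the same moments crowd participants into the first seconds of heating.

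The 3°C is therefore unsupported, and the direction of the error is unknown. With 30 per group and two-sided 0.05, the difference detectable with 80% power is 4.4°C if SD 6 is right and 2.2°C if the SD is 3. The second value assumes that 35°C is right and that a smaller SD applies. The finding is no argument for a larger sample.

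It is worth correcting because the figure is the article's only detectable difference in degrees. It is secondary to the power error: even with SD 6 accepted, power for half an SD is about 48%, not 80%.

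**What to change.** In section 2.6.4, replace the 35°C (SD 6°C) example with a mean and between-person SD that are compatible with the 30°C start, and state their source. Say which of the three defined pain levels they refer to. Recompute the detectable difference in °C at the true power for 30 versus 30, and state whether the test is one- or two-sided.

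The sponsor's pilot described in the Discussion may inform the SD if it used the same ramp, which the article does not say. Its participants were aged 65–81, so it cannot supply the younger-group mean. If no compatible values are available, drop the 3°C and give the detectable effect in SD units only, about 0.74 SD at 80% power (two-sided).

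The change costs one sentence and one recalculation, best made together with the correction of the 80% claim. Sample size and procedures are unaffected.

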Next, functional images will be aligned to each other within runs using rigid‐body coregistration in SPM 12 (Penny, Friston, Ashburner, Kiebel, & Nichols, 2007). Images will be coregistered to the T1‐weighted structural image and the transformation of the structural image to MNI space will be applied to the functional images, followed by resampling, yielding functional images at 3mm isotropic resolution. We will spatially smooth with a 6mm‐FWHM Gaussian kernel.

We will use region of interest (ROI) masks from the WFU PickAtlas tool box to delineate the anatomical boundaries for ROIs in our a priori hypotheses (Maldjian, Laurienti, & Burdette, 2004; Maldjian, Laurienti, Kraft, & Burdette, 2003). For sensory regions/lateral pathway, these are: anterior cingulate cortex, primary somatosensory cortex and secondary somatosensory cortex. For affective regions/medial pathway, these are: amygdala, periaqueductal gray, hypothalamus, pre‐frontal cortex, insula, and hippocampus.

Standard SPM12 approaches will be used to generate first‐level T‐maps. We will model activation as the contrast of a target temperature relative to baseline or relative to warmth (including ramp up and ramp down periods as covariates of no interest in the generalized linear model). These first‐level maps containing activation changes due to the temperature contrasts (mild pain > warmth, moderate pain > warmth, and moderate pain > mild pain) will be exported from SPM for hypothesis testing (Table 1).

**TABLE 1 jan14514-tbl-0001:** Index of protocol‐relevant acronyms and their meaning

3T	3 Tesla
ASL	Arterial spin labeling
BOLD	Blood oxygenation level dependent
BPISF	Brief pain inventory‐short form
CBF	Cerebral blood flow
EPI	Echo planar imaging
fMRI	Functional magnetic resonance imaging
FOV	Field of view
FWHM	Full width half maximum
HAMD	Hamilton depression scale
IRB	Institutional review board
JNP	Just noticeable pain
*M*	Mean
MNI	Montreal neurological institute
MP	Moderate pain
MRI	Magnetic resonance imaging
pCASL	pseudo‐continuous arterial spin labeling
RF	Radio frequency
ROI	Region of interest
*SD*	Standard deviation
SENSE	Sensitivity encoding
SES	Socioeconomic status
SPM 12	Statistical parametric mapping version 12
SPSS	Statistical package for social sciences
STAI	State trait anxiety inventory
STROBE	Strengthening the reporting of observational Studies in epidemiology
TE	Echo time
TFE	Turbo field echo
TR	Repetition time
WFU	Wake forest university
WP	Weak pain

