Age and sex associations with functional connectivity will be tested using the connectivity (Z) matrices for the relevant ROI for sensory and affective pain regions using the median connectivity value within the network for each subject. Linear regression analyses will be used to assess the age group effect on the overall connectivity values after co‐varying (adjusting) for regional gray matter volume and resting cerebral blood flow (CBF) as measured by pCASL generation software described below. As with the activation analyses, more specific age (years) and sex associations with activation will be assessed within each of the age groups. We will also examine the association of psychophysical data with regional brain connectivity metrics. To correct for multiple comparisons in brain imaging data we will use 3dClustSim (Cox, 1996; Cox & Hyde, 1997; Gold et al., 1998).To calculate the corrected *p* value of the brain signal in a respective ROI. This program uses the intrinsic volume and Monte Carlo simulations set at 10,000 iterations. A corrected voxel size of activation will be provided for each ROI to determine statistical significance. Data distributions will be evaluated and transformed as needed to meet the assumptions of the specific statistical methods and p‐values of 0.05 will be used for all tests.

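### The Aim 2 activation sensitivity (3.81 versus about 4.04, SD 0.46) is not delivered by 30 versus 30, and the plan does not tie the SD of 0.46 to the quantity that Aim 2 will test

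*Protocol article*

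**What the plan says.** The power statement in section 2.6.4 (Sample size estimation) opens with "Case/control groups of the size proposed in this research (30 younger adults, 30 older adults) will provide 80% statistical power" for a difference "as small as half a standard deviation in the distributions of the observed values". It applies this rule to temperature and unpleasantness, and says that the reasoning carries over to the age-group analyses of activation and connectivity. For activation it draws on two earlier ageing studies: "we can expect that our control participants may have activation values (as Z scores) with approximate *mean* = 3.81 and *SD* 0.46". It then concludes: "Given our proposed sample sizes, a respective case activation mean value of ~4.04 would be statistically significant". The same paragraph also gives a smallest significant correlation of 0.34, with activation in an ROI among its examples.

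The activation analysis is described elsewhere. Section 2.4.3 states "Standard SPM12 approaches will be used to generate first‐level T‐maps" and says that these maps are exported for hypothesis testing. Section 2.6.2 corrects for multiple comparisons by simulated cluster thresholds: "A corrected voxel size of activation will be provided for each ROI to determine statistical significance". On alpha, section 2.6 says only "All statistical significance tests will maintain Type I error rates (alpha values) of no more than 0.05"; it does not say whether tests are one- or two-sided.

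**The concern.** There are two separate difficulties. The first is that 4.04 is 3.81 plus half of 0.46, so the activation example inherits the claim that 30 per group gives 80% power for half an SD. That claim can be checked from the article's own figures.

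The second concerns the SD. The half-SD rule treats 0.46 as the spread between participants. A first-level Z is an estimate divided by its own standard error, so at a fixed voxel it varies with an SD of about 1 even if every participant has the same true activation. Put relative to the mean, scan noise alone is 1/3.81 = 26%, while the stated total spread is 0.46/3.81 = 12%. If the Aim 2 unit is a voxel-level first-level statistic, 0.46 is too small for it.

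This is the only mean difference in activation units that the plan offers. A reader could take a null activation result as evidence against a shift from 3.81 to about 4.04, when the study had at best an even chance of detecting one.

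**Working it through.** **Inputs from the article.** n = 30 per group, claimed power 80%, effect 0.5 SD, control mean 3.81, SD 0.46 and case mean about 4.04 (all section 2.6.4); alpha 0.05 (section 2.6). Two-sided testing is assumed, with one-sided results shown as well.

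**The plan's own figure.** 0.5 × 0.46 = 0.23, and 3.81 + 0.23 = 4.04. This step reproduces.

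**Power at the plan's SD.**
- Standard error of the difference: 0.46 × √(2/30) = 0.46 × 0.2582 = 0.1188.
- Noncentrality: 0.23/0.1188 = 1.94.
- Normal approximation: Φ(1.94 − 1.96) = 49%. Noncentral t on 58 df: 48%. One-sided: 61%.
- The 80% does not reproduce. It would need 63 per group by the normal formula (64 by t), or 50 if one-sided.

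**Detectable difference with 80% power.**
- (1.960 + 0.842) × √(2/30) = 0.72 SD; by the t distribution, 0.74 SD. One-sided: 0.64 SD.
- At SD 0.46: 0.74 × 0.46 = 0.34, so a case mean of 3.81 + 0.34 = 4.15.

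**Is an observed 0.23 significant?** t = 1.94 on 58 df gives p = 0.058 two-sided and 0.029 one-sided. The two-sided threshold is a difference of 0.238.

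**What SD would a Z score have?** The article gives no figure, so this was simulated.
- One fixed voxel, true Z near 3.8, noise only: SD 0.93 at 100 df, 0.97 at 250 and 0.99 at 500. Four runs of 132 volumes give 528 volumes before allowing for autocorrelation.
- Mean of voxel Z scores over an ROI, noise only: SD about 0.1 to 0.8.
- Peak Z in an ROI, noise only: SD about 0.4 to 0.85.

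The ROI results used 3 mm voxels, assumed ROIs of 27 to 1,728 voxels, and smoothness of 6 mm (the stated kernel) or 8 to 10 mm (assumed). True differences between people add to all of these.

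**Consequence for 30 versus 30 (noncentral t, two-sided 0.05).**

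| Between-person SD | Power for 0.23 | Difference at 80% power | Case mean |
|---|---|---|---|
| 0.46 (article) | 48% | 0.34 | 4.15 |
| 1.0 (voxel-level Z, noise only) | 14% | 0.74 | 4.55 |
| 1.5 (assumed, with true variation added) | 9% | 1.10 | 4.91 |

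**The case against.** Three points on the other side carry weight.

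- **The kind of Z is not stated.** A reader might infer that 0.46 cannot be a between-person SD at all. The documents do not support that. Section 2.6.4 does not call its Z scores first-level or single-voxel, and it speaks of activation in an ROI. The simulated noise SD of an ROI mean or peak can lie below 0.46. The source studies, which are not at hand, would have to settle it. What stands is narrower: sections 2.4.3 and 2.6.2 fairly read as voxelwise tests within ROI masks, because a cluster-size threshold has little meaning otherwise, and for that unit an SD of 0.46 is too small. If 0.46 describes an averaged or peak value, the plan has not linked it to what it tests.
- **It is not the only sensitivity given for Aim 2.** The paragraph extends the half-SD rule to activation and adds the correlation of 0.34. That is correct, but the half-SD rule is itself wrong for 30 versus 30, and the correlation does not address a difference between group means.
- **The sentence promises significance, not power.** Read as a threshold for an observed difference, 4.04 is close: the two-sided threshold is about 4.05, and a one-sided test would pass. But the sentence illustrates a paragraph that claims 80% power, and a true difference at the significance threshold is detected only about half the time.

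**Conclusion.** The point holds in two parts of unequal strength. The first needs no assumption about the Z scale: at the article's own SD, 30 versus 30 gives about 48% power for 0.23 (61% if one-sided), and 80% power needs about 0.34, or 0.74 SD. The second is conditional: if Aim 2 compares voxel-level first-level Z scores, as the analysis sections suggest, power for 0.23 is about 14% at best and the detectable difference is at least about 0.74 Z units. This rests on an SD of about 1, which follows from how a Z score is defined and is not stated in the article.

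It would go too far to say that 0.46 is impossible, or that 0.23 is wrong by a factor of three whatever the measure. The documents leave open which kind of Z the 0.46 describes.

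**What to change.** In section 2.6.4, replace the sentences giving 3.81, 0.46 and 4.04 with a statement that 30 versus 30 has 80% power (two-sided 0.05) for a difference of about 0.74 between-person SD in the Aim 2 activation measure. Convert this to Z or contrast units only if the SD used is the between-participant SD of the quantity that Aim 2 will compare, and say what that quantity is (voxel, ROI mean, ROI peak or ROI contrast estimate). The pilot sample of 12 men and 12 women mentioned in the Discussion may supply such an SD if its scans allow. It covers only ages 65 to 81, so the text should say that the value may not carry over to ages 30 to 89.

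The cost is a sentence or two and, at most, a small computation on pilot data. No extra participants are needed. The stated sensitivity becomes less favourable.
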